### Statistical Methods

Statistical analyses will be conducted using linear mixed models with PROC MIXED in SAS V 9.1 (SAS Institute Inc, Cary, NC) and alpha levels will be set at *p *< .05. The models will be specified to adjust for the clustered nature of the data and multiple imputations will be considered if the dropout rate is substantial. Differences between participants in the intervention and groups at baseline and differences between completers and those who drop out of the study will be examined using Chi square and independent samples t-tests in PASW Statistics 17 (SPSS Inc. Chicago, IL) software.

Focus group responses will be analysed using an inductive analysis where an initial exploration of the verbal responses will be used to identify any patterns or themes [60]. Using a recursive approach, quotes with similar meanings will be grouped together and labelled with a 'theme' [61]. A concept map will then be created to give a visual display of the themes and to aid in providing an accurate description and interpretation of the focus group data.

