### Sample Size Calculation

A battery of fitness assessments will be conducted to determine the HRF levels of participants. The primary outcome variable in this study is cardio-respiratory fitness. A power calculation was conducted to determine the sample size necessary to detect changes in cardio-respiratory fitness (VO2max). Based on a previous study by Kolle et.al (2009), an increase of 6 mL/kg/min was regarded as clinically important and achievable in children [19]. Using an alpha of 0.05 and power of 80%, a sample size of 128 will be needed to detect a 6 mL/kg/min difference between groups. To account for the clustered nature of the data and participant drop-out, we will aim to recruit 200 participants from four schools.

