### Blinding & Randomization

Participants and research assistants will be blinded to treatment conditions during baseline assessments. Randomization by school will be performed at the completion of baseline assessments and the four participating schools will be randomly assigned to the Fit-4-Fun intervention (2 schools) or a 9-month wait-list control group (2 schools). A randomization envelope will be prepared by a member of the research team and an independent third party will blindly allocate the four schools into one of the two treatment conditions.

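### With two schools per arm, the promised cluster adjustment does not secure a test of the arm effect on its 2 between-school degrees of freedom

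*Protocol article*

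**What the plan says.** Under Blinding & Randomization, the protocol article states "Randomization by school will be performed at the completion of baseline assessments", and that "the four participating schools will be randomly assigned to the Fit-4-Fun intervention (2 schools) or a 9-month wait-list control group (2 schools"). The school is therefore the randomised unit.

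Under Statistical Methods it states "Statistical analyses will be conducted using linear mixed models with PROC MIXED in SAS V 9.1", that "alpha levels will be set at" p < .05, and that "The models will be specified to adjust for the clustered nature of the data". It names no random effects, no denominator-df method and no ICC.

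Under Sample Size Calculation it states "Using an alpha of 0.05 and power of 80%, a sample size of 128 will be needed to detect a 6 mL/kg/min difference between groups". The recruitment target is then raised to 200 children from four schools, to allow for clustering and drop-out together. No SD, ICC or drop-out rate is given.

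**The concern.** A mixed model with a school effect accounts for clustering in the standard error, but with four schools the validity of the test turns mainly on the reference distribution. The two-sided 5% critical value is 4.303 on 2 df and about 1.97 on child-level df. Which one applies depends on how the school effect is coded and which df method is chosen, and the article fixes neither.

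A second difficulty is that with four schools the school variance is often estimated as zero. The standard error then reverts to one that ignores school.

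The Discussion expects the trial to settle whether the program is effective enough for large-scale use. A chance difference between two pairs of schools, reported at a nominal 5%, could be taken as that evidence.

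**Working it through.** **Inputs from the article:** 4 schools, 2 per arm; 200 children recruited, so 200/4 = 50 per school; 128 in the power calculation, so 128/4 = 32 per school; alpha 0.05; difference 6 mL/kg/min; planned power 80%.

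**Assumptions:** two-sided testing (sidedness is not stated); ICC from 0 to 0.10 and beyond; SD 12 mL/kg/min; equal school sizes; one follow-up comparison without baseline adjustment.

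**1. The plan's own figure.** The SD is not given, so 128 cannot be reproduced from the stated inputs alone. With SD 12, n per arm = 2 × (1.960 + 0.842)² × (12/6)² = 62.8, so 63 per arm and 126 in total. A t-based calculation gives 64 per arm, 128 in total, with power 0.801. The figure therefore fits an SD of about 12 and a test that counts children as independent.

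**2. ICC implied by the inflation.** 200/128 = 1.5625. If all of this were design effect, ICC = (1.5625 - 1)/(50 - 1) = 0.0115. This is the most the planners' allowance covers, since part of it is for drop-out. It says nothing about the true ICC.

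**3. Type I error.** Let m be children per school, ρ the ICC and total variance 1. The between-school mean square (MSB, 2 df) has expectation (1 - ρ) + mρ. The within-school mean square (MSW, 4(m - 1) df) has expectation 1 - ρ. The arm difference has variance [(1 - ρ) + mρ]/m. With the school variance bounded at zero, the REML standard error uses MSB when it exceeds MSW, and the pooled mean square otherwise. One million null trials per setting, tested on child-level df, gave:

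| ICC | 50 per school | 32 per school | School variance estimated as zero (50 per school) |
|---|---|---|---|
| 0 | 3.7% | 3.7% | 63% |
| 0.01 | 7.0% | 5.9% | 48% |
| 0.05 | 13.7% | 11.6% | 24% |
| 0.10 | 16.2% | 14.8% | 14% |

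The limit for large ICC has a closed form. For t on 2 df, P(|T| > c) = 1 - c/√(2 + c²). At c = 1.97 this is about 18.7%; at 1.96 it is 18.9%.

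**4. The same trials on 2 df.** If the school variance may go negative, the error is 5.0% at every ICC. If it is bounded at zero, the test is very conservative with 50 per school: 0.1% at ICC 0.02, 0.8% at 0.05 and 2.0% at 0.10. A rule that uses 2 df when the variance estimate is positive and child-level df when it is zero gives 5.3% at ICC 0.01, 7.4% at 0.05 and 6.9% at 0.10. It does not fully protect the level either.

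**5. Power on 2 df.** Noncentrality = 6/(12 × √[(1 + 49ρ)/50]), critical value 4.303:

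- ICC 0: 6/1.697 = 3.54, power 48%
- ICC 0.01: 6/2.072 = 2.90, power 37%
- ICC 0.05: 6/3.152 = 1.90, power 20%

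With 32 per school the figures are 36%, 29% and 18%.

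**6. Randomisation distribution.** There are C(4,2) = 6 ways to allocate the schools, so the smallest two-sided randomisation p-value is 2/6 = 0.33. Any p < .05 from this trial rests on the model and its df.

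**The case against.** The strongest reply is that the article does not prescribe the wrong test. It promises cluster adjustment, names the school as the randomised unit and acknowledges clustering in the recruitment target. Random-effect coding and the df method are details that a condensed article may leave to the full analysis plan, and that plan may already use 2 df. This stands as far as it goes: a reader might infer that the trial will run at a false-positive rate of 13 to 16%, and the documents do not support that. Such a rate needs child-level df, an ICC of about 0.05 to 0.10 and about 50 children per school. At the largest ICC that the recruitment inflation could imply, the figure is about 7%; at ICC 0 the test is slightly conservative.

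The simulation also covers only a single follow-up comparison. For an arm-by-time test over the three assessments, what matters is how much schools vary in change. That was not simulated.

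Two further inferences should not be drawn. Nothing in the article proposes class as the clustering level. Nor is an unstated baseline covariate an error: an article may omit it, and a model over three time points can carry baseline as an outcome.

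The reply does not dispose of the point, however. A general cluster-adjusted mixed model is not enough with four schools, and the one statement about power that the article does make is built on child counts and does not fit a 2-df test.

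**Conclusion.** The point holds as a gap in what the stated method secures. The design fixes 2 between-school df for the arm effect. The analysis sentence is compatible both with a valid test and with one whose type I error runs from about 4% to 19%, depending on an ICC that the article does not give. The error exceeds 5% once the ICC passes about 0.005 with 50 per school (5.4% at that value).

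The consequence for power does not depend on guessing the coding. A valid 2-df test reaches at most about 48% with SD 12 and 50 per school, against the planned 80%. The SD is back-solved from 128, and the ceiling is at ICC 0. The type I error figures further assume two-sided testing and equal school sizes.

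**What to change.** In Statistical Methods, state that the arm effect is tested on 2 between-school df, by one of two routes:

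- a school-level analysis, comparing school summaries with a t-test on 2 df; or
- a mixed model with school nested in arm, the arm test set to 2 df, and the school variance not bounded at zero.

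If the primary test is an arm-by-time contrast, say that the same df apply to it. Adjustment for each child's baseline value is optional.

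Report the four school-level results beside the model estimate, and describe p-values from four schools as not confirmatory. In Sample Size Calculation, restate the power for a 2-df test, with the SD and ICC assumed.

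The cost is a few sentences and a few lines of code. For the same standard error, confidence intervals become about 4.303/1.97 = 2.2 times as wide, and the stated power becomes much less favourable. Analysis wording makes the test honest; it does not cure having only two schools per arm.

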## Discussion

The Fit-4-Fun study described in this paper is one of the first RCTs in Australia to specifically target the HRF levels of primary school children. The results of this study will provide further evidence to support the feasibility and efficacy of the Fit-4-Fun intervention for improving the HRF and PA levels of children, along with their attitudes towards physical fitness.

This study addresses some of the limitations found in previous interventions by: (1) specifically targeting all of the components of HRF in primary school children; (2) taking a multi-faceted approach to facilitating behaviour change via the HPS Framework; (3) having a theoretically- and curriculum-based program; (4) extending HRF education beyond the classroom and into the home; and (5) by using enjoyable and engaging learning activities to motivate students to adopt healthy behaviours.

The findings of this study will provide valuable information for other research groups looking to improve the HRF levels of children via school-based interventions. Furthermore, it will ascertain whether the Fit-4-Fun program is an effective program for future large-scale implementation.
